# Effectiveness of robot-assisted virtual reality mirror therapy for upper limb motor dysfunction after stroke: study protocol for a single-center randomized controlled clinical trial

**DOI:** 10.1186/s12883-022-02836-6

**Published:** 2022-08-22

**Keywords:** Upper limb motor dysfunction, Stroke, Robot-assisted virtual reality mirror therapy (RAVRMT), Randomized controlled trial, Functional magnetic resonance imaging (fMRI)

## Abstract

**Background:**

Upper limb motor dysfunction is a common sequela of stroke, and its clinical efficacy needs to be improved. This protocol describes a trial to verify the clinical efficacy of robot-assisted virtual reality mirror therapy (RAVRMT) in improving upper limb motor dysfunction in stroke patients, and to explore the central mechanism by using functional magnetic resonance imaging (fMRI).

**Methods:**

This trial will be a single-center, assessor-blinded, randomized controlled clinical study. Thirty-two eligible patients will be randomly divided into 2 groups according to the ratio of 1:1, namely virtual reality mirror therapy (VRMT) group and robot-assisted virtual reality mirror therapy (RAVRMT) group. The interventions will be performed once a day for 4 weeks. Primary outcome is Fugl–Meyer motor function assessment-Upper Extremity (FMA-UE), secondary outcomes are the Montreal Cognitive Assessment (MoCA), activities of daily living (ADL), quality of life (QOL), the pain visual analogue scale (VAS-pain) and fMRI. Adverse events will be recorded, and severe adverse events will be used as criteria to discontinue the intervention.

**Discussion:**

Combined application of robot-assisted therapy and virtual reality mirror therapy could theoretically activate mirror neuron system and reward circuits to a greater extent, but further high-quality research is needed. The results of this trial will determine whether RAVRMT could better improve upper limb motor dysfunction after stroke and explore its central mechanism using fMRI.

**Trial registration:**

This trial was prospectively registered at ClinicalTrials.gov (ChiCTR2200061721; 01 July 2022).

## Background

In recent years, stroke has become the second leading cause of death and the third leading cause of disability in the world [1]. Studies have shown that about 80% of acute stroke patients and more than 55% chronic stroke patients have upper limb motor dysfunction [2, 3], which seriously affects the quality of life of patients and their families [4, 5]. At present, the conventional rehabilitation methods for upper limb motor dysfunction after stroke consists of physical therapy [6], occupational therapy [7], but more than 50% of stroke patients still have long-term upper limb motor dysfunction [8]. The clinical efficacy of conventional rehabilitation methods in the treatment of upper limb motor dysfunction after stroke is not satisfactory, and new rehabilitation concepts and techniques are urgently needed.

How can we better promote the recovery of upper limb motor dysfunction after stroke? The disruption of motor-related brain networks is the primary cause of upper limb motor dysfunction after stroke, and another important cause is the upper limb disuse caused by long-term inactivity, so a single treatment for one cause is not adequate [9]. In stroke, the disruption of motor-related brain networks is the damage at the central level [10] and the upper limb disuse caused by long-term inactivity is the damage at the peripheral level [11]. As a clinical central intervention technology, mirror therapy can activate the motor-related brain network through action observation [12]. A recent meta-analysis demonstrates that mirror therapy can significantly improve upper limb motor dysfunction in stroke patients [13]. As a new kind of mirror therapy, virtual reality mirror therapy (VRMT) can provide immersion mirror therapy for stroke patients [14]. However, mirror therapy lacks the participation of proprioception [15], which may not be able to simulate the actual scene well and activate the motor-related brain network to the greatest extent. As a clinical peripheral intervention technology, a large number of studies have proved that robot-assisted therapy (RAT) can have a positive impact on the recovery of upper limb motor dysfunction in stroke patients through programmed task training [16, 17], including motor function and proprioception. At present, more and more studies show that mirror therapy combined with other interventions is superior to a single rehabilitation therapy in the treatment of upper limb motor dysfunction in stroke patients [18–20].

In this study, we designed a device that combined RAT and immersion VRMT to treat upper limb motor dysfunction after stroke. Moreover, the device can dynamically match the motion trajectory of the RAT with the motion images displayed in real time by the VRMT, so as to realize the cycle of “visual information input-visual information output-motion feedback” in the stroke patient. This is different from other combinations of a central intervention and a peripheral intervention for upper limb motor dysfunction after stroke [21, 22], which a central intervention and a peripheral intervention do not dynamically match each other in real time. In summary, the device is an innovative medical rehabilitation machine, which realizes the cycle of “visual information input-visual information output-motion feedback”, and provides patients with a full-body immersive experience that is consistent with vision, touch, and proprioception. We call the treatment robot-assisted virtual reality mirror therapy (RAVRMT) and the device RAVRMT robot. The RAVRMT robot is ultimately expected to activate mirror neuron system (MNS) and reward circuits to the greatest extent possible, thereby promoting the improvement of upper limb motor dysfunction in patients after stroke.

Therefore, we designed a randomized controlled trial to explore the clinical efficacy of RAVRMT in improving upper limb motor dysfunction in patients after stroke. Meanwhile, in this trial, functional magnetic resonance imaging (fMRI) scans will be performed to find significant changes in motor-related brain functional connectivity, and the motor-related brain functional network will be compared before and after the intervention to further reveal the brain neural mechanism of RAVRMT’s effects.

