### Inclusion criteria

The Inclusion criteria include the following: (1) Diagnosis of stroke by clinical assessment and neuroimaging as defined by the International Classification of Diseases (ICD-11); (2) Regardless of gender, age between 30 and 70; (3) Hemiplegic; (4) Primary stroke, stroke course of 1–6 months; (5) Primary school or above, with normal cognitive function (Montreal Cognitive Assessment (MoCA) score of 26 or above); (6) Sufficient audiovisual level to complete necessary research examinations and virtual reality mirror therapy; (7) Patient’s informed consent.

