### Assessment

The study period for each patient is 12 weeks. All patients will be assessed before and after a 4-week intervention for FMA-UE, MoCA, ADL, QOL, VAS, fMRI and safety measures. At week 8 after the end of 4-week intervention, all patients will be assessed their FMA-UE, MoCA, ADL, QOL, and VAS. All outcomes will be measured by assessors who have been uniformly trained, blinded to the randomization group after the baseline visit assessment.

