fMRI is a non-invasive imaging technique that uses magnetic resonance to measure changes in brain hemodynamics caused by neuronal activity to reflect the activation state of brain regions. The fMRI scans of this study are acquired on a 3-Tesla scanner (SIEMENS VERIO, Erlangen, Germany) in the Yueyang Hospital of Integrated Traditional Chinese Medicine and Western Medicine. In the study, we acquire resting-state fMRI and T1-weighted image scans. Patients will be asked to lay supine in the scanner with their eyes closed but remain awake, and their heads are immobilized with foam pads to minimize head motion. The resting-state fMRI are acquired with the following parameters: repetition time (TR) = 2000 ms, echo time (TE) = 30 ms, flip angle (FA) = 90°, field of view (FOV) = 256 mm*256 mm, matrix = 256*256, slice thickness = 3 mm (no gap) and number of slices = 33. The 3D T1-weighted images are acquired using a brain volume sequence with the following parameters: TR = 1900 ms, TE = 4.6 ms, FA = 9°, FOV = 256 mm*256 mm, matrix = 256*256, slice thickness = 1 mm (no gap) and the number of slices = 160. After data preprocessing, the following indicators can be obtained: Amplitude of Low Frequency Fluctuation (ALFF), regional homogeneity (ReHo), Functional Connectivity (FC), Independent Component Analysis (ICA). ALFF is an effective method to reflect local brain activity by detecting low frequency (0.01–0.1 Hz) fluctuations of the blood oxygen level dependent (BOLD) signal [28]. ReHo reflects the correlation between the time series of a given voxel and that of its neighbors [29]. FC reflects the correlation between different brain regions [30]. ICA is an algorithm of multiple regression analysis, which distinguishes the components of the brain’s resting state network from one of the confounding components [31].

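### The fMRI mechanism aim rests on a before-after comparison, names no RAVRMT-versus-VRMT contrast, and speaks of activation that a resting scan cannot show

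*Protocol article*

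**What the plan says.** **Hypothesis.** The Background expects much of the device: "The RAVRMT robot is ultimately expected to activate mirror neuron system (MNS) and reward circuits to the greatest extent possible". The Discussion part of the Abstract makes the claim comparative: the combination "could theoretically activate mirror neuron system and reward circuits to a greater extent". The main Discussion repeats this.

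**Stated imaging comparison.** The Background says that "the motor-related brain functional network will be compared before and after the intervention to further reveal the brain neural mechanism", and the sentence goes on to attribute that mechanism to RAVRMT. It names motor-related connectivity and networks as the target. This is the only fMRI comparison stated in the article.

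**Measurement.** Under Secondary outcomes, "we acquire resting-state fMRI and T1-weighted image scans", with patients asked to "lay supine in the scanner with their eyes closed but remain awake". The indices are ALFF, ReHo, functional connectivity and ICA.

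**Who is scanned.** The Assessment section covers both arms: "All patients will be assessed before and after a 4-week intervention for FMA-UE, MoCA, ADL, QOL, VAS, fMRI and safety measures".

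**Setting.** Inclusion requires "Primary stroke, stroke course of 1–6 months". Both arms receive conventional therapy, which the trial records but does not control, and both use the same device with mirrored virtual images.

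**Tests.** The Statistical analysis section introduces its methods as being for the clinical data. It gives paired tests within groups and a repeated-measures ANOVA between groups, at one-sided 0.05. It does not mention fMRI.

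**The concern.** A claim that one therapy engages certain circuits more than another needs a comparison of the two therapies. The comparison that the Background links to RAVRMT's mechanism is one over time. In the first months after stroke, brain networks may change because of recovery, background rehabilitation or the mirror content that both arms share. A before-after change in the RAVRMT arm contains all of these plus any effect of the robot.

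There is also a gap between the wording of the hypothesis and the measurement. The main Discussion defines the mirror neuron system by what activates when an action is performed or observed. Neither happens in an eyes-closed resting scan. The reward circuits, the other part of the hypothesis, are not named as the target of any fMRI measure.

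At stake is the interpretation of a listed secondary outcome for which every patient is scanned twice. A shared change could be reported as the mechanism of RAVRMT, and the comparative question could go unanswered although the data to address it exist.

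**Working it through.** **1. What each comparison contains.** Write the mean change from baseline to week 4 in a resting-state measure as a sum of parts:

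- RAVRMT arm: recovery + conventional therapy + virtual mirror content + what the robot adds
- VRMT arm: recovery + conventional therapy + virtual mirror content

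The before-after change in the RAVRMT arm estimates the whole first line. Randomisation makes the shared parts equal in expectation, so the difference between the lines estimates what the robot adds. Only that difference speaks to a greater effect than VRMT.

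**2. What the scan can show, against the hypothesis.**

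| Element of the hypothesis | What the protocol plans | Match |
|---|---|---|
| Activation | Resting-state indices, eyes closed, no task | Indirect: resting change, not activation during therapy |
| Mirror neuron system | Motor-related networks | Partial: the Discussion describes three of the four listed regions as involved in motor execution |
| Reward circuits | No fMRI measure directed at them | None stated |
| To a greater extent | Before-after comparison | Not tested by that comparison |

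**3. Illustration of size.** The documents give no fMRI change or SD, so there is no plan figure to reproduce. Inputs:

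- n = 13 per arm (required number) and n = 16 (recruited number), from Sample size.
- One-sided 0.05, from Statistical analysis. Applying it to fMRI is an assumption, since that section does not mention fMRI.
- A shared shift g, in SDs of the change score, equal in both arms: assumed.
- RAVRMT-specific effect: zero, assumed.
- One normally distributed measure, tested in the direction of the shift: assumed.

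The probability that the paired test in the RAVRMT arm is significant is P(T > t), where t is the upper 5% point of the t distribution with n − 1 degrees of freedom and T is noncentral t with noncentrality g√n.

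| g | g√13 | P, n = 13 | g√16 | P, n = 16 |
|---|---|---|---|---|
| 0.3 | 1.08 | 0.27 | 1.20 | 0.31 |
| 0.5 | 1.80 | 0.52 | 2.00 | 0.60 |
| 0.8 | 2.88 | 0.86 | 3.20 | 0.92 |
| 1.0 | 3.61 | 0.96 | 4.00 | 0.985 |

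For the between-arm contrast the shared shift cancels (g − g = 0), so P stays at 0.05 for every g.

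With a two-sided 0.05 test, the chance of significance in the direction of the shift is 0.38 (n = 13) and 0.47 (n = 16) at g = 0.5, and 0.75 and 0.85 at g = 0.8. The between-arm contrast then stays at 0.025 in that direction.

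**The case against.** The strongest reply is that the before-after reading comes from one sentence in the Background. That sentence does not restrict the comparison to the RAVRMT arm or exclude a group comparison. fMRI is an outcome of a randomised two-arm trial, and all patients are scanned at both times. The repeated-measures ANOVA could be read as covering the imaging indices, and the detailed imaging plan may sit in a full protocol or analysis plan that is not shown.

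Much of this stands. A reader might infer that the imaging has no control, or that natural reorganisation is bound to be reported as RAVRMT's mechanism. The documents support neither: the control scans are planned, and a between-group test is described that could be applied to them. Missing imaging detail, such as a list of regions, is no fault in an article. What remains is a stated inference. The text ties a before-after comparison to RAVRMT's mechanism, and the section that does name a group comparison introduces it for the clinical data.

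A second reply is that resting-state connectivity does measure the stated aim of finding changes in motor-related connectivity, and that activation is offered as device rationale, hedged as an expectation or a theory. This also stands in part. A reader might infer that the scan is irrelevant to the hypothesis, or that the mirror neuron system is left out. Neither follows: resting-state indices bear on these networks indirectly, and most of the listed mirror neuron regions overlap with motor regions. The clear gap in target is the reward circuits.

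Finally, the percentages rest on assumed shifts. At 0.3 SD they fall to 27 to 31%, so a significant before-after result is not a near certainty.

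**Conclusion.** The concern holds in a limited form. The only fMRI comparison stated cannot separate RAVRMT from recovery, conventional therapy or the shared mirror content, and it does not test the comparative hypothesis. The scan supports a statement about resting-state activity and connectivity, not about activation during therapy. No imaging measure is directed at the reward circuits.

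For assumed shared shifts of 0.5 to 0.8 SD and no RAVRMT-specific effect, a one-sided before-after test is significant in about 52 to 86% of trials at 13 per arm and 60 to 92% at 16, against 5% for the between-arm contrast. These figures depend wholly on the assumed shift. The argument about what each comparison contains does not.

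Severity is minor to moderate. The objective is secondary and exploratory; the FMA-UE primary outcome and the sample size are not affected. The imaging objective remains answerable, because both arms are scanned at both times.

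**What to change.** - In the Background and in the fMRI outcome description, state that the mechanism conclusion rests on the RAVRMT-minus-VRMT difference in baseline-to-week-4 change in the resting-state measures already planned. Label before-after changes within each arm as descriptive.
- Word the conclusion as resting-state change, not activation, wherever the text says what this trial will show. Activation can remain as rationale.
- Rest any statement about reward circuits on the same contrast in striatal regions, or drop it.
- Optional: name a short set of regions in advance, and relate imaging change to FMA-UE change.

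**Cost.** Text and analysis only; no new scan or task. The downside is power. For an effect of δ SDs of change with n per arm, the noncentrality is δ√n for the before-after test and δ√(n/2) for the between-arm contrast, a ratio of 1/√2, or about 0.71. With 13 to 16 patients per arm a null imaging contrast would be weak evidence, and the report should say so.

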## Methods and design

### Study design

This is a single-center, assessor-blinded, randomized controlled clinical trial. This trial was approved by the Ethics Committee of Yueyang Hospital of Integrated Traditional Chinese Medicine and Western Medicine. In this trial, a randomized controlled study will be used, and all eligible patients will be randomly divided into 2 groups according to the ratio of 1:1, namely VRMT group and RAVRMT group. There will be a 4-week intervention and a 12-week follow-up. Outcome measurements include the Fugl-Meyer motor function assessment -Upper Extremity (FMA-UE), fMRI, and others. The flowchart of this trial is shown in Fig. 1.

**Fig. 1 Fig1:**
[figure not shown]
Flowchart of study design. W, week

### Recruitment

Patients will be recruited from the Yueyang Hospital of Integrated Traditional Chinese Medicine and Western Medicine. The study started in June 2022; the end date is planned in June 2023 (Chinese Clinical Trial Registry, ChiCTR2200061721). We advertise the study online (website) and offline (poster) to recruit patients. To enhance recruitment quality, investigators monitor medical records. The attending doctor will carefully inquire and record the patients’ past and present medical history.

### Inclusion criteria

The Inclusion criteria include the following: (1) Diagnosis of stroke by clinical assessment and neuroimaging as defined by the International Classification of Diseases (ICD-11); (2) Regardless of gender, age between 30 and 70; (3) Hemiplegic; (4) Primary stroke, stroke course of 1–6 months; (5) Primary school or above, with normal cognitive function (Montreal Cognitive Assessment (MoCA) score of 26 or above); (6) Sufficient audiovisual level to complete necessary research examinations and virtual reality mirror therapy; (7) Patient’s informed consent.

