### Randomization and allocation

Randomization is conducted by an independent investigator who is not involved in the recruitment, assessment, treatment, or data analysis. The randomization sequence is generated by computer-generated random numbers. Thirty-two eligible patients are randomly divided into VRMT group and RAVRMT group in a ratio of 1:1. The assignment of patients is concealed in an opaque, sealed envelope, and cases are numbered by an independent investigator in the order of entry into the group. Before starting an intervention, inform therapists of the patient’s specific number and intervention information in order to obtain the assigned treatment.

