### Primary outcome

The primary outcome of this study is the mean change in FMA-UE scores between and within the two groups before and after the intervention and follow-up. FMA-UE is widely used in the assessment of upper limb motor function and can reflect the level of upper limb motor function in stroke patients. The total score of the upper limb is 66 points, which is divided into three parts: shoulder–arm (36 points), wrist–hand (24 points), and coordination (6 points), and lower scores indicate worse upper limb movement function. The FMA-UE is often used as the gold standard to test the validity of other scales [9, 25]. FMA-UE has excellent reliability and validity and is sufficiently sensitive to clinical and research practice [20].

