### Statistical analysis

Blind the statistician. The clinical data will be analyzed by SPSS25.0 software. For the measurement data of the obtained data, the normality test is first performed. For the measurement data conforming to the normal distribution, it is expressed as the mean ± standard deviation (x ± s). The paired t test is performed before and after the two groups, and the comparison between the two groups is used Two-way repeated measures analysis of variance (2-way repeated measures ANOVA) test. The non-normally distributed measurement data before and after a group of self-comparison uses the Wilcoxon signed rank test, and comparison between the two groups uses the Mann-Whitney signed rank test. The significance level of the statistical test is set to α = 0.05, and the one-sided test is performed. A data monitoring committee will not be implemented because all participants will be treated and adverse events are expected to be low.

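### Time since stroke, 1 to 6 months at entry, is used neither in the allocation as described nor in the stated between-group FMA-UE analysis, which costs precision and leaves a chance imbalance uncorrected.

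*Protocol article*

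**What the plan says.** Under Inclusion criteria, the protocol article admits patients with "Primary stroke, stroke course of 1–6 months". Time since stroke is not mentioned again as a design or analysis variable.

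Under Randomization and allocation, "The randomization sequence is generated by computer-generated random numbers" and "Thirty-two eligible patients are randomly divided into VRMT group and RAVRMT group in a ratio of 1:1". Assignments are held in opaque sealed envelopes. No stratum, block or minimisation factor is named.

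The primary outcome is "the mean change in FMA-UE scores between and within the two groups before and after the intervention and follow-up". The Assessment section adds that "The study period for each patient is 12 weeks".

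Under Statistical analysis, for normally distributed data "the comparison between the two groups is used Two-way repeated measures analysis of variance". For other data, "comparison between the two groups uses the Mann-Whitney signed rank test". Neither is given a covariate, and a Mann-Whitney test cannot take one.

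**The concern.** With a 12-week study period, a patient who enters at month 1 is observed to about month 4 after stroke, and one who enters at month 6 to about month 9. It is plausible that the natural gain in FMA-UE differs between these two stretches. A group-by-time ANOVA removes a difference between arms in starting level. It does not remove a difference in expected gain, which is how time since stroke would act on a change score.

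With 16 patients per arm, chance differences in time since stroke are common. Two things are at stake. Variation in natural recovery stays in the error term and costs precision. And if the arms turn out unbalanced, the stated analysis has no means of allowing for it, while a covariate added after the imbalance has been seen would be post hoc.

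**Working it through.** **Yardsticks from the plan (Sample size section).** The planning difference is 30.41 − 23.00 = 7.41 points. The pooled SD is √[(9.07² + 5.58²)/2] = √56.70 = 7.53. With 16 per arm, the standard error of the difference is 7.53 × √(2/16) = 2.66. The SD is that of FMA-UE scores; the SD of change is not given. The plan has no figure of its own on time since stroke to reproduce.

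**Assumptions (not in the documents).** Half of the patients, 16 of 32, count as early entrants. Early entrants gain D = 3, 5 or 8 points more than late entrants, whichever arm they are in.

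**How often the arms are unbalanced.** With 16 per arm and 16 early patients, the number X of early patients in one arm is hypergeometric: P(X = k) = C(16,k)² / C(32,16). The arms differ by |2X − 16|, so a difference below 4 means X = 7, 8 or 9.
- C(32,16) = 601,080,390
- C(16,8)² + 2 × C(16,7)² = 165,636,900 + 261,747,200 = 427,384,100
- P(difference of 4 or more) = 1 − 427,384,100/601,080,390 = 0.289

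**Shift in the contrast and variance share.** A difference of 4 early patients shifts the contrast by D × 4/16. The share of variance that the factor could explain is D² × 0.5 × 0.5 / 56.70.

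| D (assumed) | Shift (points) | Share of 7.41 | In standard errors | Variance share |
|---|---|---|---|---|
| 3 | 0.75 | 10% | 0.28 | 4% |
| 5 | 1.25 | 17% | 0.47 | 11% |
| 8 | 2.00 | 27% | 0.75 | 28% |

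**Check with a continuous factor.** Assume instead that entry times are uniform over 1 to 6 months and that the gain falls by 1, 2 or 3 points per month of later entry. Total SD is held at 7.53. The variance of entry time is 25/12, so the SD of the between-arm difference in mean time since stroke is √(25/12 × 2/16) = 0.51 months. Simulation puts that difference above 0.5 month in 33% of allocations and above 1 month in 5%. An unadjusted t test was compared with ANCOVA on time since stroke, at one-sided 0.025 with 16 per arm:

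| Slope (points/month) | R² | Power for 7.41, unadjusted | Power for 7.41, adjusted |
|---|---|---|---|
| 1 | 0.04 | 77% | 77% |
| 2 | 0.15 | 77% | 82% |
| 3 | 0.33 | 77% | 90% |

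Averaged over all allocations, the unadjusted false-positive rate is about 2.5% at every slope. Given an imbalance above 1 month, the picture changes:
- If it favours RAVRMT, the unadjusted false-positive rate is about 7%, 11% or 25%.
- If it disfavours RAVRMT, unadjusted power for 7.41 points is about 64%, 45% or 27%.
- Adjusted false-positive rates in the same allocations lie between about 1.4% and 3.6%. Each rests on about 500 simulated trials, so the spread is largely simulation noise.

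**The case against.** **Randomisation already deals with this.** A concurrent randomised control separates natural recovery from treatment in expectation, and chance imbalance is already part of the standard error. This stands. A reader might infer that the trial is biased, or that its false-positive rate is inflated. The documents do not support that: the overall error stays nominal, and the distortion is conditional on an unlucky draw.

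**The recovery premise has no figure behind it.** This also stands. A reader might take the Background statement that "about 80% of acute stroke patients and more than 55% chronic stroke patients have upper limb motor dysfunction" as proof of large recovery inside the entry window. It is not. The two figures are prevalences with two citations, the second is only a lower bound, neither is broken down within months 1 to 6, and neither is in FMA-UE points. Time since stroke is therefore called a plausible predictor here and no more.

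**The shifts are modest.** They are. At 0.28 to 0.75 standard errors, an imbalance of 4 patients would not by itself produce a 7.41-point effect, and at 1 point per month adjustment gains no power. The variance shares also borrow an SD of scores for a change outcome.

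**An unseen analysis plan may add the covariate.** It may, and silence alone would be no finding. But the article does state its allocation method and its between-group tests, and the point concerns those stated choices. Unstratified randomisation is valid, so the lack of stratification is the lesser part.

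**Conclusion.** The point holds as a matter of efficiency and of robustness to an unlucky allocation. It is not a threat to the validity of the test. A variable that must be established for eligibility, and that plausibly predicts change in FMA-UE, is left out of the stated analysis of a 32-patient trial.

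Under the assumption of 16 early patients, an imbalance of 4 or more arises in 29% of allocations. A difference of 4 then moves the estimate by 0.75 to 2.0 points if early entrants gain 3 to 8 points more. The gain from adjustment ranges from none to 13 percentage points of power (77% to 90%) over the assumed slopes. All of these sizes rest on recovery rates that the documents do not give and on the SD of scores, so they show a range and are not estimates for this trial.

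**What to change.** Prespecify time since stroke as a continuous covariate, together with baseline FMA-UE, in the between-group FMA-UE analysis, for example an ANCOVA or a mixed model. Let that model carry the comparison, because the Mann-Whitney alternative cannot use a covariate. Fix this before any outcome is seen. If an unpublished analysis plan already does so, only the article's stated analysis needs to be brought into line.

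The cost is about one degree of freedom per covariate: with 32 patients, a two-group comparison of change goes from 30 to 28. No patient, visit or measurement is added.

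Stratifying the list by time since stroke, with concealed permuted blocks, is a secondary step and applies only if no patient has been allocated. The Recruitment section says the study began in June 2022, while Trial status says that recruitment has not begun, so this must be settled first. If allocation has started, keep the existing list and make only the covariate change. Otherwise the added cost is a new list and one envelope set per stratum.
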